### Sample size

Based on a previous electroacupuncture study on gastric emptying function, the response rate is approximately 50–70% [26–30]; however, the data of sham electroacupuncture are insufficient. Thus, we assumed that the response rates of the TEA group and sham-TEA group were 50% and 20%, respectively. Therefore, Δ is 30%. We estimated the sample size using the following formula:
$$ n=\frac{2{\left({\mu}_{\alpha }+{\mu}_{\beta}\right)}^2P\left(1-P\right)}{\Delta ^2} $$

A sample size of 66 patients will give us a power of 90% (*β* = 0.1) with a two-sided significance level of 0.05 (*α* = 0.05). To compensate for a 20% expulsion rate, a total of 90 patients will be required for the study. We will design a ratio of 2:1 (60 patients in the TEA group, 30 patients in the sham-TEA group) based on the response rates of the two groups.

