### Randomization

All eligible patients will be randomly assigned to the TEA group or the sham-TEA group by an allocation ratio of 2:1, and the framework of the trial is assumed as superiority (Fig. 2). The randomization process will be achieved by opening sealed envelopes with computer-generated random numbers by the SPSS 22.0 software. The process will be implemented by a researcher who is not involved in the data collection or analysis.

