### Statistical analysis

Sensitivity analysis will be performed to determine the impact of incomplete records on the results. Intent-to-treat analysis of the results will be performed if there is nonadherence or missing data. Only two data statisticians will have access to the final trial dataset, which will only contain coded data, and they will perform statistical analysis using the SPSS version 22.0 software. Student’s *t* test will be performed to assess the difference in the measurements (the residual rates of radioactivity in the stomach at 45, 60, 75, 90, 105, and 120 min) between the TEA group and the sham-TEA group. Paired Student’s *t* test will be used to compare the differences in serum albumin, NE, TNF-α, IL-1β, IL-6, glucose, LF/HF (sympathovagal ratio), and QoL at baseline and 4 weeks after intervention in each group. The *χ*^2^ test will be used for categorical data such as the PG-SGA, HADS, and adverse events. Univariate and multivariate analyses with multiple linear regression will be used to identify independent predictors of outcome measures. The results will be aggregated as median values. *P* values of < 0.05 will be considered as statistically significant.

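### The 66 evaluable patients for 90% power do not follow from the protocol's own formula and rates; after the planned 20% loss, the 90-patient 2:1 trial has about 71–73% power on response rate

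*Protocol article*

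**What the plan says.** The calculation is in the Sample size section of the protocol article.

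- **Rates:** "we assumed that the response rates of the TEA group and sham-TEA group were 50% and 20%, respectively". The difference follows: "Therefore, Δ is 30"%.
- **Formula:** n = 2(μα + μβ)²P(1 − P)/Δ². The text does not define P or say whether n is per group or in total.
- **Result:** "A sample size of 66 patients will give us a power of 90"% (β = 0.1), "with a two-sided significance level of 0.05".
- **Allowance for loss:** "To compensate for a 20% expulsion rate, a total of 90 patients will be required for the study".
- **Allocation:** "We will design a ratio of 2:1 (60 patients in the TEA group, 30 patients in the sham-TEA group").

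The Randomization section also gives the 2:1 ratio and adds that "the framework of the trial is assumed as superiority". The total response rate is listed as a primary outcome, and it is the only outcome used to size the trial. The Statistical analysis section names the chi-square test for categorical variables: the "test will be used for categorical data such as the PG-SGA, HADS, and adverse events".

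**The concern.** All the inputs are printed, so the result can be checked directly, and three things fail. The formula does not return 66 for these inputs. It is the equal-arms formula, while the design is 2:1, and unequal allocation costs power at a fixed total. The inflation from 66 to 90 does not match a 20% loss under either usual convention.

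At stake is how the result will be read. The protocol claims a 10% risk of missing a 30-point difference. If the true risk is well above that, a non-significant comparison would be taken as fairly strong evidence against the assumed effect when it is not.

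**Working it through.** **Inputs** (Sample size section): p₁ = 0.50, p₀ = 0.20, Δ = 0.30, two-sided α = 0.05 (z = 1.960), β = 0.1 (z = 1.282), 20% loss, 60:30 randomised. The test is taken as the uncorrected chi-square test, following the Statistical analysis section's rule for categorical data.

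**Step 1. The printed formula.** (1.960 + 1.282)² = 10.507.

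- P = 0.35 (simple mean of the two rates): n = 2 × 10.507 × 0.35 × 0.65 / 0.09 = 53.1 per group, so 54 + 54 = 108.
- P = 0.40 (mean weighted 2:1): n = 2 × 10.507 × 0.40 × 0.60 / 0.09 = 56.0 per group, so 57 + 57 = 114.
- P = 0.50 (where P(1 − P) is largest): n = 2 × 10.507 × 0.25 / 0.09 = 58.4.

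The unstated P cannot rescue the figure. Read per group, n never reaches 66. Misread as a total, it is still at most 59. A total of 66 does come out of the formula with one-sided α, 80% power and P = 0.40 (32.97, so 33 per group), but that contradicts the stated two-sided 0.05 and 90%.

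**Step 2. The size for the actual 2:1 design.** With k = 2 and pooled P = 0.40, the sham arm needs

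n₀ = [1.960 √(P(1 − P)(1 + 1/k)) + 1.282 √(p₁(1 − p₁)/k + p₀(1 − p₀))]² / Δ² = 38.4, so 39.

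The TEA arm then needs 78, giving 117 evaluable. Exact enumeration of the chi-square test at 78:39 gives 90.8% power.

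**Step 3. The loss adjustment.** 66/0.8 = 82.5 and 66 × 1.2 = 79.2; neither is 90. In the other direction, 90 × 0.8 = 72, or 48:24 if loss is proportional.

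**Step 4. Power for 50% vs 20%.** The normal approximation is Φ[(Δ − 1.960 s₀)/s₁], where s₀ is the pooled and s₁ the unpooled standard error. At 48:24, s₀ = 0.1225 and s₁ = 0.1090, so (0.30 − 0.2400)/0.1090 = 0.55 and the power is 70.9%.

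| Evaluable (TEA:sham) | Normal approx. | Exact chi-square | Fisher |
|---|---|---|---|
| 66 (44:22) | 66.7% | 66.6% | 64.3% |
| 72 (48:24) | 70.9% | 72.6% | 70.2% |
| 90 (60:30) | 80.9% | 81.7% | 78.3% |

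Even 66 patients split 33:33 give only 73.5% (normal approximation) or 75.4% (exact chi-square).

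**Step 5. Sensitivity at 48:24** (exact chi-square). The section itself says sham data are insufficient, so the sham rate is varied. The 25% and 30% values are my assumptions. The TEA rates of 60% and 70% lie in the 50–70% range that the section cites.

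| TEA vs sham | Power |
|---|---|
| 50% vs 20% | 73% |
| 50% vs 25% | 55% |
| 50% vs 30% | 38% |
| 60% vs 20% | 93% |
| 70% vs 20% | 99% |

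**The case against.** The strongest reply is that 71–73% is one scenario. It supposes that the whole 20% leaves the analysis, evenly from both arms. The Statistical analysis section provides for intent-to-treat analysis when there is nonadherence or missing data, and the Quality control section promises to keep collecting data after discontinuation. If all 90 are analysed, power is about 82% and the risk of missing the effect is 18%, under twice the stated 10%. This is fair as to the range, although the Blinding section removes unblinded participants from the final analysis and the sample size itself plans for the loss. It does not restore 90%: no analysis set from 90 patients reaches it at the stated rates.

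The test for response rate is inferred, since the chi-square sentence does not name that outcome. At 48:24 other choices run from 62% (Yates correction) to 79% (unpooled Wald approximation). The figure moves, but all of these are well below 90%.

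The cited studies also allow a TEA rate above 50%, and at 60% vs 20% the trial would be adequately powered. That is true, but the protocol fixed 50% and claimed 90% for it. A balanced sensitivity table should show both directions.

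Finally, response rate is only one of the primary outcomes. Nothing here bears on the power of the scintigraphy comparisons.

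**Conclusion.** The concern holds. The 66-patient figure cannot be obtained from the printed formula at the stated rates, alpha and power, and 90 does not follow from 66 with a 20% loss. For the response-rate comparison at 50% vs 20%, power is about 71–73% with 72 evaluable patients and about 82% with all 90. The type II risk is thus 27–29% after the planned loss, nearly three times the stated 10%, and 18% with no loss. These figures assume an uncorrected two-sided chi-square test at 0.05 and, for 72 patients, proportional loss across arms. The error is in stated figures, so it is not a matter of detail left to another document.

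**What to change.** Rewrite the sample size paragraph:

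- Replace the equal-arms formula with a two-proportion formula for 2:1 allocation, and define P and n.
- Delete the 66-patient figure and the step from 66 to 90.
- State that 90 patients randomised 60:30 give about 82% power with no loss and about 71–73% with 20% loss, for 50% vs 20% at two-sided 0.05, and name the test assumed.
- Add a short table of power over sham rates of 20–30%, with a row for a higher TEA rate from the cited 50–70% range.

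I would not keep the 90% by searching for a larger difference that yields it, because that fits the assumption to the sample size. For scale, true 90% power at the stated rates and 2:1 would need 117/0.8 = 146.25, so 147 randomised.

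The cost is the wording of one paragraph and a less favourable stated power. No extra patients are needed.

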### Data management and monitoring

The attending doctor who has performed the gastrectomy will be responsible for obtaining informed consent. Each participant will be required to sign an informed consent form and questionnaires and record personal information during the trial. The researchers will confirm the original data, collect all data on clinical outcomes very accurately, and store the data in the database safely. Clinical data will be carefully preserved using electronic and printed CRFs. To guarantee data quality, only outcome assessors will access the CRFs. Except for the researchers and the members of the ethics committee, people unrelated to the trial are not allowed to obtain access to CRFs. The personal information of the patients will not be disclosed in the public presentation. The data will only be used for this study. Biological specimens will be collected, stored, and analyzed in the current trial, and they are not intended for future use in ancillary studies. All data associated with the trial will be uploaded to the database of our hospital, and it will be monitored thoroughly by the Medical Ethics Committees.

### Statistical analysis

Sensitivity analysis will be performed to determine the impact of incomplete records on the results. Intent-to-treat analysis of the results will be performed if there is nonadherence or missing data. Only two data statisticians will have access to the final trial dataset, which will only contain coded data, and they will perform statistical analysis using the SPSS version 22.0 software. Student’s *t* test will be performed to assess the difference in the measurements (the residual rates of radioactivity in the stomach at 45, 60, 75, 90, 105, and 120 min) between the TEA group and the sham-TEA group. Paired Student’s *t* test will be used to compare the differences in serum albumin, NE, TNF-α, IL-1β, IL-6, glucose, LF/HF (sympathovagal ratio), and QoL at baseline and 4 weeks after intervention in each group. The *χ*^2^ test will be used for categorical data such as the PG-SGA, HADS, and adverse events. Univariate and multivariate analyses with multiple linear regression will be used to identify independent predictors of outcome measures. The results will be aggregated as median values. *P* values of < 0.05 will be considered as statistically significant.

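### The primary residual rates are compared with a t test that ignores the baseline scan, and intent-to-treat is offered as the answer to missing data while the Blinding section removes patients from the analysis

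*Protocol article*

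**What the plan says.** Statistical analysis section, on incomplete data: "Sensitivity analysis will be performed to determine the impact of incomplete records on the results", followed by "Intent-to-treat analysis of the results will be performed if there is nonadherence or missing data". No method is attached to either sentence.

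The same section, on the primary scintigraphy outcome at six times from 45 to 120 minutes: "Student’s *t* test will be performed to assess the difference in the measurements" between the two arms. No baseline term is mentioned. Baseline values enter only through paired t tests within each arm, for serum markers, the LF/HF ratio and quality of life.

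Elsewhere in the article:
- **Inclusion criteria:** patients must have a scintigraphic half-emptying time above 70 minutes, so each has a scan before treatment.
- **Sample size:** "To compensate for a 20% expulsion rate, a total of 90 patients will be required for the study".
- **Dropout criteria:** poor compliance counts as dropping out, as does voluntary withdrawal.
- **Blinding:** a patient who is unblinded leaves the trial, and that patient's data are flagged and kept out of the final analysis.
- **Quality control:** for patients who discontinue or deviate, the team will still gather what data it can.

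**The concern.** There are two linked faults in what the article states.

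First, intent-to-treat is used as if it were a way to handle missing data. It fixes the analysis population and the arm in which each patient counts. It cannot create a 4-week scan that was not done. The article also contradicts itself on that population: one section promises intent-to-treat, and another takes out patients because of something that happened after randomisation.

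Second, the named primary test does not use the strongest predictor the trial will have of the 4-week scan, namely the same patient's scan before treatment. With up to 90 patients split 2:1, that wastes precision. It also leaves the comparison open to a selection that baseline adjustment would largely correct: if slow emptiers leave one arm more than the other, the remaining patients are no longer comparable at baseline, and an unadjusted test counts that difference as treatment effect.

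**Working it through.** **Inputs from the article.** 60 TEA and 30 sham-TEA; 20% loss allowed for; two-sided 0.05; a baseline scan required for inclusion. The article gives no figure for bias or for the precision of this test, so there is none to reproduce.

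**Assumptions, not in the article.** Residual rates on a standardised scale (SD 1 in each arm); the inclusion scan yields the same residual rates as the 4-week scan; correlation ρ = 0.6 between them; 20% of 4-week scans missing in each arm, leaving 60 × 0.8 = 48 and 30 × 0.8 = 24.

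**Standard error.** The t test has SE = √(1/48 + 1/24) = 0.25 SD. Baseline adjustment multiplies this by √(1 − ρ²) = √0.64 = 0.8, giving 0.20 SD.

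**Precision under random loss.** For an assumed true effect of 0.6 SD, effect/SE is 0.6/0.25 = 2.4 for the t test and 0.6/0.20 = 3.0 for the adjusted model. Simulated power is 66% and 83%.

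**Bias when loss in the TEA arm depends on baseline.** Let the probability of loss be p(x) = 1/(1 + exp(1.65 − x)), where x is the baseline residual rate in SDs. This is log-odds 1 per SD, and the constant 1.65 sets the mean loss at 20%. The mean baseline of those still observed is ∫ x φ(x)[1 − p(x)] dx / 0.8 = −0.173. The bias of the t test is ρ × (−0.173) = 0.6 × (−0.173) = −0.104 SD, which favours TEA because a lower residual rate means faster emptying. As a false-positive rate: 0.104/0.25 = 0.42 standard errors, and Φ(−1.96 + 0.42) + Φ(−1.96 − 0.42) = 0.062 + 0.009, about 7%.

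**Simulation with no true effect, patients with a 4-week scan only:**

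| Loss depends on | t test: bias in favour of TEA, false positives | Adjusted for baseline |
|---|---|---|
| baseline, TEA arm only | 0.10 SD, 7% | 0.00 SD, 5% |
| baseline, TEA arm only, half as strongly | about 0.06 SD, 5% | 0.00 SD, 5% |
| baseline, equally in both arms | 0.00 SD, 5% | 0.00 SD, 5% |
| baseline, opposite directions in the two arms | 0.21 SD, 13% | 0.00 SD, 5% |
| 4-week value, TEA arm only | 0.17 SD, 11% | 0.11 SD, 9% |

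Both columns use the same patients, so the improvement comes from adjusting for baseline and not from counting more patients.

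**Range over the assumed correlation** (first row of the table): the bias is ρ × 0.173, or 0.05, 0.10 and 0.14 SD at ρ = 0.3, 0.6 and 0.8. The SE factor √(1 − ρ²) is 0.95, 0.80 and 0.60.

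**The case against.** The strongest reply is that the t test is valid in a randomised comparison, that details of missing-data handling usually sit in an analysis plan not shown here, and that the scenarios are chosen. Much of this stands. With no loss, or with loss that acts alike in both arms, the t test is unbiased. The opposite-direction scenario is deliberately adverse, and nothing in a patient-blinded trial suggests it. At half the assumed dependence the false-positive rate hardly moves. The absence of an imputation method is not a fault of a journal article.

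The conditional wording is also less harmful than it looks: the condition covers exactly the situations in which intent-to-treat makes a difference.

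A reader might go further and infer that the result labelled intent-to-treat would be a complete-case comparison of about 72 of 90 patients. The article does not support that. Nowhere does it say that patients without a 4-week value are dropped; a t test or χ² test can follow imputation, and a missing response can be counted as non-response. Nor is the 20% allowance a forecast of 20% missing scans: poor compliers count as dropouts but can still be scanned, and the Quality control section promises continued data collection. For the same reasons no definite inflation of the response-rate difference can be claimed.

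The reply does not reach two things that the article positively states: an unadjusted test for a primary outcome with a baseline scan to hand, and an exclusion that contradicts intent-to-treat. The planned multiple linear regression does not fill the gap, since its stated purpose is to find predictors and not to make the primary comparison.

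**Conclusion.** The point holds in a limited form. The article misuses intent-to-treat as a response to missing data, contradicts it in the Blinding section, and fixes a less efficient and less robust primary test than its own data allow.

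The loss of precision does not depend on any dropout mechanism: at a correlation of 0.6 the standard error is 25% larger than with adjustment (0.25 against 0.20 SD). The bias is conditional. It is about 0.10 SD with 7% false positives if loss depends on baseline in the TEA arm only at the assumed strength, nil if dependence is the same in both arms, and only partly removed by adjustment if loss follows the 4-week value itself (0.17 SD falling to 0.11 SD). The correlation, the loss pattern and the equal 20% loss per arm are all assumptions. This is a worthwhile improvement to the plan; it does not show that the planned result would be wrong.

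**What to change.** 1. Replace the conditional sentence with a statement that the primary analysis includes all randomised patients in their assigned arm, whether or not there is nonadherence or missing data.
2. Reconcile the Blinding section with this, so that the analysis population is the same in both places. Whether an unblinded patient continues treatment is a separate matter for the investigators.
3. Replace the t test for residual rates with a model adjusted for the baseline scan: ANCOVA at each time, or a mixed model over the scan times. Both are available in SPSS 22.
4. Say that scans obtained after discontinuation, as foreseen under Quality control, enter this analysis.

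The cost is a few sentences and a little more analysis work. No visits, scans or patients are added, provided the residual rates from the inclusion scan are kept. Adjustment does not restore patients who have no 4-week scan, so obtaining those scans remains the main protection if loss follows the outcome itself.

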### Inclusion criteria

All allocated patients met the following inclusion criteria: (1) 18–80 years old, (2) gastric cancer patients considered to have DGE (a half-life gastric emptying by gastric scintigraphy greater than 70 min), (3) within 3–6 months after distal gastrectomy, (4) no gastrointestinal obstruction before surgery, and (5) TNM staging < IV, no distant metastasis.

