### Outcome measures

#### Primary outcome measures

##### Gastric emptying function

We will evaluate the gastric emptying function of these postoperative patients who visit outpatient clinics. Gastric scintigraphy will help us to evaluate the gastric emptying function and has the advantages of being noninvasive and painless. ^99m^Tc tin colloid will be mixed with a semisolid diet of 200 g of rice gruel with a boiled egg. Radioactive signs will be recorded from diet intake to 120 min afterward, and the residual rates of radioactivity in the stomach at 45, 60, 75, 90, 105, and 120 min will be calculated by a half-life of 9 mTc. We will compare the recorded residual rates and the time to 50% residual rate between the two groups as the primary outcomes.

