Gastric scintigraphy is the gold standard method for the diagnosis of gastroparesis and DGE, but there is no uniform approach due to the differences in the composition, volume, and calories of the meal; the protocol of monitoring; and the analysis of data during the examination [36]. The definition of DGE after gastrectomy is not well addressed or studied. We defined DGE as a half-life of gastric emptying greater than 70 min according to previous studies [9, 37]. Tougas et al. chose a low-fat meal consisting of ^99m^Tc-labeled and scrambled eggs, two slices of bread, strawberry jam (30 g), and water (120 ml); anterior and posterior images were taken at times of 1 min, 60 min, 120 min, and 240 min in all patients, and the distribution of percent gastric residual retention at different time points was analyzed in 123 volunteers [38]. Similarly, Tomita et al. mixed ^99m^Tc tin colloids with a semisolid diet of 200 g of rice gruel with a raw egg. A gastric emptying curve was drawn based on the residual rate of radioactivity in the stomach [9]. Kim et al. used ^99m^Tc tin colloid-raidolabeled boiled eggs, and DGE was defined if a half-time of emptying was over 72 min [37]. In our trial, such a radioisotope method with endoscopy will be used to evaluate the gastric emptying function of these postgastrectomy patients. We will have ^99m^Tc tin colloid mixed with a semisolid diet of 200 g of rice gruel with a boiled egg, which is more in line with the appetites of Chinese people.

Gastric dysfunction after distal gastrectomy may be associated with damage to a gastric pacemaker (located at the junction between the fundus and the body of the greater curvature) and truncal vagotomy [39, 40]. Some studies reported that Roux-en-Y reconstruction could result in Roux-en-Y stasis syndrome due to the destruction of natural small-bowel pacemakers [20–22]. Kim et al. found that DGE was associated with laparoscopic operation and duration of the postoperative period [37]. Chong et al. revealed that gastric emptying within a week after distal gastrectomy was markedly slower in Billroth-I than in Billroth-II, while gastric emptying at 3–6 months showed no difference between the two groups [41]. Accordingly, it is necessary for subgroup analysis of different types of operations.

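### The primary residual rates are compared by t tests that leave out the entry scintigraphy; adjusting for it is a free gain in precision

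*Protocol article*

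**What the plan says.** - **Primary test.** In Statistical analysis, a Student's t "test will be performed to assess the difference in the measurements (the residual rates of radioactivity in the stomach" is applied "at 45, 60, 75, 90, 105, and 120 min) between the TEA group and the sham-TEA group". Neither a baseline covariate nor a change score is mentioned.
- **Primary scintigraphic outcomes.** Under Gastric emptying function: "We will compare the recorded residual rates and the time to 50% residual rate between the two groups as the primary outcomes".
- **Baseline scan.** Inclusion criteria require "a half-life gastric emptying by gastric scintigraphy greater than 70 min".
- **Other analyses.** The paired t tests in Statistical analysis are within-group and cover serum markers, LF/HF and quality of life, not the residual rates. The only regression reads: "Univariate and multivariate analyses with multiple linear regression will be used to identify independent predictors of outcome measures". Subgroup analyses by reconstruction and by surgical access are planned under Total response rates, and the Discussion says that "it is necessary for subgroup analysis of different types of operations".
- **Arms.** Patients are assigned "by an allocation ratio of 2:1", 60 to TEA and 30 to sham-TEA, with a 20% loss allowed for (Sample size).
- **Summary measure.** "The results will be aggregated as median values" (Statistical analysis).

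**The concern.** A patient's emptying before treatment is likely to predict emptying after it. A comparison that ignores a baseline value leaves that predictable variation in the error term, so the interval is wider and the power lower than the same patients could give. With 30 sham patients, or 24 after the assumed loss, this matters.

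Two smaller points attach to the same sentence. Student's t pools the variance, and with unequal arms its level depends on the two spreads being equal. And a t test concerns means, whereas the section's general sentence on summaries speaks of medians, so it is unclear which effect estimate will stand beside the P value.

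**Working it through.** **Inputs from the protocol.** Arms 60 and 30; loss 20%, so 60 × 0.8 = 48 and 30 × 0.8 = 24; two-sided α = 0.05. I take the scan after the 4-week intervention as the one compared.

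**Inputs that are assumed.** The protocol gives no SD, effect size or baseline correlation for the residual rates, and Data Availability reports no pilot data. I assume an effect d = 0.6 SD, a baseline to week-4 correlation r = 0.3 to 0.6, and sham/TEA SD ratios from 0.5 to 2.

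**Plan's own figure.** There is none for the residual rates. The 66 patients in Sample size are for the response rate. With its stated α and power, the plan's formula gives 2 × (1.960 + 1.282)² × 0.35 × 0.65 / 0.30² = 53.1, so 54 per arm and 108 in all. That is a separate matter, and nothing below depends on it.

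**Step 1, precision.** Adjusting for baseline multiplies the error variance by 1 − r², which is worth 1/(1 − r²) − 1 more patients. The noncentrality of the unadjusted test is d × √(48 × 24 / 72) = 0.6 × 4 = 2.40 on 70 df; after adjustment it is 2.40/√(1 − r²). The one degree of freedom spent on the covariate costs less than 0.1 percentage point.

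| r | 1 − r² | Worth in patients | Noncentrality | Power |
|---|---|---|---|---|
| none (plan) | 1.00 | – | 2.40 | 65.8% |
| 0.3 | 0.91 | +10% | 2.52 | 69.9% |
| 0.4 | 0.84 | +19% | 2.62 | 73.3% |
| 0.5 | 0.75 | +33% | 2.77 | 78.0% |
| 0.6 | 0.64 | +56% | 3.00 | 84.1% |

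**Step 2, where r is likely to lie.** Admitting only half-emptying times above 70 min narrows the baseline range and lowers r. In simulation, if the slowest 30% to 50% are admitted, a full-range correlation of 0.5 falls to about 0.28 to 0.33, and one of 0.7 to about 0.45 to 0.51. The lower rows of gain are therefore the more plausible.

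**Step 3, level of the pooled-variance test at 48:24.** With the TEA SD set to 1 and the sham SD to s, the true variance of the difference is 1/48 + s²/24. The test assumes [(47 + 23s²)/70] × (1/48 + 1/24).

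- s = 1.25: 0.0859 against 0.0741, ratio 1.16. The level is about 2Φ(−1.96/√1.16) = 6.9%.
- s = 0.8: 0.0475 against 0.0551, ratio 0.86. The level is about 3.5%.

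Simulation (100,000 runs) agrees:

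| Sham/TEA SD | Student | Unequal-variance t |
|---|---|---|
| 0.5 | 1.8% | 5.0% |
| 0.67 | 2.7% | 5.0% |
| 0.8 | 3.5% | 5.0% |
| 1 | 5.1% | 5.0% |
| 1.25 | 6.8% | 5.0% |
| 1.5 | 8.4% | 4.9% |
| 2 | 11.1% | 5.0% |

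**The case against.** The strongest reply is that an unadjusted comparison is valid under randomisation. Its standard error already allows for chance imbalance, and covariates are often left to an analysis plan. The first part stands: this is lost precision, not bias. The second carries less weight here, because the protocol is not silent; it names the test. Neither the regression, framed as a search for predictors, nor the subgroups supply an adjusted treatment comparison.

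A reader might infer that 2:1 allocation makes the t test unsafe. The document does not support that. With equal SDs the level stays at 5%, and it rises only if the smaller sham arm is the more variable. No SDs are given. If the 50% and 20% response rates acted as a mixture of responders and non-responders with a common spread within each class (an assumption), the sham/TEA SD ratio would lie between √(0.16/0.25) = 0.8 and 1, and the test would be conservative.

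Three further limits stand.

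- The inclusion criterion states a half-emptying time. That the entry scan also yields the six residual rates is a fair inference, but the schedule figure is not shown.
- The value of adding reconstruction type is not known. The Discussion itself cites a study in which Billroth-I and Billroth-II did not differ at 3 to 6 months, which is this trial's entry window. That randomisation is unstratified can only be read from silence in a condensed article.
- The sentence on medians is general. It does not exclude reporting mean differences, so it needs clarifying and is not an error in itself.

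**Conclusion.** The point holds as a free improvement. The stated test for the residual rates ignores a baseline measurement that entry guarantees in some form. For an assumed correlation of 0.3 to 0.6 the loss equals about 10% to 56% more patients, or 66% power instead of about 70% to 84% at 48:24 with an assumed 0.6 SD effect; the lower end is the more likely. Neither the correlation nor the effect comes from the document, so the size is illustrative while the direction holds whenever baseline and follow-up correlate.

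The pooled variance is a secondary weakness. The level is about 3.5% to 6.8% for SD ratios of 0.8 to 1.25, and about 2.7% to 8.4% for 0.67 to 1.5, while an unequal-variance test holds 5%. This is sensitivity to an unstated condition, not a shown inflation. Nor do these figures show that the trial is underpowered for the residual rates, since it was sized on response rates alone. Multiplicity across the six times is a separate matter.

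**What to change.** Replace the t tests on the residual rates by a baseline-adjusted comparison at 4 weeks: either ANCOVA at each time, or one repeated-measures model with arm, time, arm-by-time, the baseline residual rate and reconstruction type. If residual rates were not recorded at entry, use the baseline half-emptying time as the covariate. Allow arm-specific variance or use robust standard errors.

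Analyse time to 50% residual rate, which is also primary, in the same way with its own baseline value. Recording stops at 120 min, so the plan should say how a patient still above 50% at that point is handled.

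Report adjusted mean differences with 95% CI, and keep medians as description only.

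Cost: analysis wording and slightly more programming. No new scans, visits or data are needed.
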